**Fig. 2 Fig2:**
[figure not shown]
Schedule of enrolment, interventions and assessments

### Data analysis

Intention-to-treat analysis will be performed using SPSS Advanced Statistics version 24.0 (SPSS, Chicago, IL, USA). Descriptive statistics will be used to summarise the demographic data; binary outcomes will be summarised with a relative risk (RR) and 95% confidence intervals (CIs) and compared between the two groups using a χ^2^ test (or Fisher’s exact test where applicable). Comparison of the number of patients with keloid formations within groups and between the two groups will be done using a χ^2^ test. A *t* test will be used to assess continuous non-skewed variables; these will be presented as means with standard deviations. For skewed ordinal data, the Mann–Whitney *U* test will be used; these data will be presented as medians with interquartile ranges. Difference in the effect over the sub-groups will be assessed using logistic regression. Outcomes of interest will be number of patients with keloid formation, changes in the appearance and specification of the keloid scar, depression, anxiety, stress and patient’s satisfaction. Changes in the appearance and specification of the keloid scar after the intervention will be summarised into two groups (binary outcome: 0 = changed, 1 = not changed) and will be analysed using logistic regression adjusting for the number of keloids formed and demographic variables. A *p* < 0.05 will be considered statistically significant.

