#### Depression, Anxiety and Stress Scale-21 (DASS-21)

The DASS-21 is the short version of the DASS-42 questionnaire. It contains a set of three self-report scales and will be used to measure anxiety, depression and stress during pregnancy and after childbirth. The DASS-21 has been shown to have high internal consistency and to yield meaningful discriminations in a variety of settings. It should meet the needs of both researchers and clinicians who wish to measure current state or change in state over time on the three dimensions of depression, anxiety and stress. The tool has been used in previous studies on perinatal women in Australia, Canada, Chile, England, Germany, Iceland, New Zealand and the USA with reasonable response rates [14, 15]. Each of the three DASS-21 scales contains 7 items. The Depression scale assesses dysphoria, hopelessness, devaluation of life, self-deprecation, lack of interest/involvement, anhedonia and inertia. The Anxiety scale assesses autonomic arousal, skeletal muscle effects, situational anxiety and subjective experience of anxious affect. The Stress scale is sensitive to levels of chronic non-specific arousal. It assesses difficulty relaxing, nervous arousal and being easily upset/agitated, irritable/over-reactive and impatient. Respondents are asked to use 4-point severity/frequency scales to rate the extent to which they have experienced each state over the past week. Scores for Depression, Anxiety and Stress are calculated by summing the scores for the relevant items and then multiplying each scale score by 2. Then, each score can be transferred to the DASS profile sheet, enabling comparisons to be made between the three scales and also giving percentile rankings and severity labels as shown in the following table.

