### Follow-up

The follow-up period consists of 12 months face-to-face visits (Fig. 1). Post-operation, the patients will be visited daily on the ward for any signs of potential infectious local complications of the treatment and immediate side effects of the medication injection until the discharge home. The patients will then be visited in the women’s health clinic at the hospital for their 6th week post-partum check. The next follow-up times will be 6 months and 12 months post caesarean section. At each follow-up visit, the same assessment and scoring scales will be used to evaluate the changes to the keloid scar. Late side effects of the medication injection as well as symptoms of depression, anxiety and stress, and participants’ satisfaction will be assessed during follow-up visits at 6 weeks, 6 months and 12 months post-partum. The participants will also be asked if they would recommend such a procedure to another woman with a caesarean section keloid scar (yes/no) and if they would repeat the experience again in a future pregnancy (yes/no).

All measurements at baseline and follow-up visits will be performed by the same researcher, who will also make all efforts to ensure compliance with follow-up. As part of continuous clinical care, patients with any residue keloid scar with be given information on further treatment including referral to plastic surgeons if they are interested (Fig. 2).

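### The only form stated for the DASS-21 outcomes is the percentage of women affected, and no stated analysis uses the pregnancy score, so much of the collected information may go unused

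*Protocol article*

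**What the plan says.** All references are to the protocol article.

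- **Scale.** The DASS-21 section describes three scales of seven 4-point items. Scores are "calculated by summing the scores for the relevant items and then multiplying each scale score by 2". A table divides each scale into five severity bands.
- **Timing.** The instrument "will be used to measure anxiety, depression and stress during pregnancy and after childbirth". Under Follow-up, late side effects "as well as symptoms of depression, anxiety and stress", together with satisfaction, "will be assessed during follow-up visits at 6 weeks, 6 months and 12 months post-partum". Each woman should therefore have one score before treatment and three after it.
- **Outcome form.** The Secondary outcomes section gives one form for these measures, the percentage of women with each condition. It names no mean score or change in score.
- **Analysis.** Under Data analysis, "binary outcomes will be summarised with a relative risk (RR) and 95% confidence intervals (CIs) and compared between the two groups" by a χ² test, or Fisher's exact test where applicable. A t test "will be used to assess continuous non-skewed variables". Skewed ordinal data go to a Mann–Whitney test, and "these data will be presented as medians with interquartile ranges". Depression, anxiety and stress then appear in a list of outcomes with no test attached.
- **Adjustment.** The one outcome with named covariates is scar change, "analysed using logistic regression adjusting for the number of keloids formed and demographic variables".

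**The concern.** A percentage of women is a yes/no variable for each woman. Read together, the Secondary outcomes and Data analysis sections send DASS-21 to an unadjusted two-by-two comparison. This has two costs.

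First, cutting the score discards graded change. If the cut lies at or below the lower edge of the moderate anxiety band, a woman who moves from 20 or more to 10–14 counts as no benefit. If it lies exactly at that edge, a woman who moves from 10 to 8 counts as full benefit. The document's own wording is about degree: the Hypothesis section expects symptoms to decline, and the DASS-21 section recommends the scale for measuring change over time.

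Second, a woman's own pregnancy score is the obvious predictor of her later score. Leaving it out wastes precision and lets a chance imbalance between arms in antenatal symptoms pass into the result.

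At stake is how a null psychological result would be understood. The depression scale serves a stated secondary objective, and an analysis with low power for a moderate effect cannot show that there is none.

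**Working it through.** **The plan's own figure.** The protocol gives no sample-size or power figure for DASS-21. Its total of 150, set for the primary outcome (45% v 70%, 80% power, two-sided 5%), reproduces: 68 per arm with continuity correction, and 68 × 1.1 = 74.8, so 75 per arm. That supplies the 75 per arm used below.

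**Assumed inputs (none is in the protocol).** Share of women above the cut, q = 15–30%. Correlation of pregnancy and follow-up scores, r = 0.3–0.7. Underlying score roughly normal.

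**Step 1: cost of cutting the score.** The efficiency of a yes/no split relative to the score is φ(z)² / [q(1 − q)], where z is the normal quantile with upper tail q.

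| q | z | φ(z) | Efficiency |
|---|---|---|---|
| 15% | 1.036 | 0.233 | 0.426 |
| 20% | 0.842 | 0.280 | 0.490 |
| 30% | 0.524 | 0.348 | 0.576 |

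**Step 2: cost of omitting the pregnancy score.** Baseline adjustment multiplies the residual variance by 1 − r². The share of information kept by the unadjusted percentage comparison, against the adjusted score at one visit, is efficiency × (1 − r²).

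- Lowest: 0.426 × (1 − 0.49) = 0.217, a loss of 78%.
- Middle (q = 20%, r = 0.5): 0.490 × 0.75 = 0.367, a loss of 63%. The 150 women then count as 0.367 × 150 ≈ 55.
- Highest: 0.576 × (1 − 0.09) = 0.524, a loss of 48%.

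With q = 10–50% the loss runs from 42% to 82%.

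**Step 3: all three visits.** With equal correlations between all occasions and the same effect at each visit, a baseline-adjusted mean of three visits has variance factor (1 + 2r)/3 − r². At q = 20% and r = 0.5 the share kept is 0.490 × (0.667 − 0.25) = 0.204, a loss of 80%. Over q = 5–50% and r = 0.3–0.7 the loss is about 72% or more.

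**Step 4: illustrative power.** Take 75 per arm, a true reduction of 0.4 SD and 20% of controls affected. The intervention share is Φ(−0.842 − 0.4) = 10.7%.

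- Percentages: pooled share 0.1535. Standard error under the null √(2 × 0.1535 × 0.8465/75) = 0.0589, and under the alternative √[(0.160 + 0.0956)/75] = 0.0584. Then (0.093 − 1.96 × 0.0589)/0.0584 = −0.38, so power is about 35%.
- Unadjusted score: 0.4 × √(75/2) = 2.45, and 2.45 − 1.96 = 0.49, so about 69% (68% by simulation).
- Adjusted score, r = 0.5: 2.45/√0.75 = 2.83, and 2.83 − 1.96 = 0.87, so about 81% (79–80% by simulation).

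With 67 per arm (75 less 10%) the three figures are 32%, 64% and 76%.

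**Step 5: if scores are not normal.** Simulated power at 75 per arm, 0.4 SD latent shift, q = 20%, r = 0.5:

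| Score shape (assumed) | χ² | t test | Baseline-adjusted linear model |
|---|---|---|---|
| Normal | 35% | 68% | 79% |
| 40% of scores at the floor | 36% | 56% | 65% |
| Floor and moderate right skew | 36% | 47% | 55% |
| Floor and strong right skew | 35% | 40% | 45% |

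The advantage of the adjusted linear model falls from 44 percentage points to 10. With strong skew and 30% affected it is 6 (42% v 48%), and the unadjusted t test gains almost nothing (43%).

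**The case against.** The strongest reply is that the protocol does not confine the comparison to percentages. Data analysis offers three routes and assigns none to depression, anxiety and stress, while the DASS-21 section explains how the numeric scores are formed. A comparison of scores therefore remains possible. This stands: a reader might infer that the arms will be compared on percentages and nothing else, and the text does not support that.

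It can also be said that a condensed article with no SAP on view may leave covariates for a secondary outcome to the SAP. This stands in part. It cannot be asserted that the pregnancy score will go unused, only that no stated analysis uses it. But the article does fix an outcome form and a test for that form, and it names covariates for scar change. The routes it lists for scores, the t test and the Mann–Whitney test, are unadjusted two-group comparisons. A better method for data already collected can therefore be named, and the point is more than a missing detail.

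Third, the size rests on assumptions. This stands. A floor at zero is plausible for a scale with a wide normal band, and it narrows the power gap considerably, although a rank-based analysis would recover some of it.

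Finally, a percentage above a recognised severity band is a legitimate and readable secondary endpoint. That is a reason to keep it as description.

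**Conclusion.** The point holds, as a matter of method for secondary outcomes. The sole stated form of the DASS-21 outcomes is a percentage, its stated test is unadjusted, and none of the listed analyses draws on the pregnancy score. This applies equally to all three scales, including depression, the one named in the secondary objectives.

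Against a baseline-adjusted score analysis at one visit, the loss is about 48–78% for 15–30% affected, correlation 0.3–0.7 and roughly normal scores, with 63% in the middle case. A reader might conclude that well over half the information is certainly lost. The documents do not support that: they give no prevalence, correlation or score distribution, and the lower end of the range is just under half. The power contrast of about 35% against 81% belongs to the normal-score case and shrinks with floor effects and skew.

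The primary result and the sample size are not affected. The change is worth making because it is nearly free.

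**What to change.** In Data analysis, state that each DASS-21 scale score (depression, anxiety and stress) is compared between arms with a linear model containing arm and the same scale's pregnancy score, reported as an adjusted mean difference with 95% CI. Name the visit in advance, such as 12 months, or specify a repeated-measures model over the three visits. State that robust standard errors or a rank-based version will be used if scores are strongly skewed. Align the Secondary outcomes wording with this, and keep the percentages by severity band as a descriptive table.

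The cost is a change of wording only, with no new data, visits or participants. The small downside is that a mean difference in points is less immediately readable than a percentage, which the descriptive table offsets.

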### Participants

The inclusion criteria for the study are (1) age between18–45 years old; (2) being pregnant at the time of recruitment; (3) presence of a keloid scar from a previous caesarean section; (4) planned caesarean section for the current pregnancy. Women of all ethnicities with a keloid scar following a previous caesarean section will be eligible to participate in the study.

The exclusion criteria for the study are (1) being primigravida and (2) having a previous caesarean section with no keloid scar. Since the aim of the study is to investigate the impact of treatment on the caesarean section keloid scar, the type of skin excision in the caesarean section (vertical or horizontal) will not be an inclusion/exclusion criterion.

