### Sample size

Using the estimates from the study by Khalid et al. [13], the intervention will increase the incidence of efficacy of treatment for keloid scarring from 45% in the excision followed by radiation group to 70% in the excision followed by intralesional triamcinolone acetonide and 5-fluorouracil group. We calculated that a total of 150 patients (75 in each group) would provide 80% power with a two-sided significance level of 5% to detect this difference between the groups. This allows for 10% non-compliance.

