### Procedures

All eligible women will be approached at the time of booking into the clinic for caesarean section at around 36 weeks and will be given information about the study. Those women who meet the inclusion criteria and sign the informed consent form will be randomised to either the intervention or the control group by the independent researcher as explained previously (Fig. 1). On the day of the caesarean section, the sealed envelope containing instructions for the type of treatment will be picked up by the surgeon. The surgeon opens the envelope when the woman is ready for the caesarean section.

The control group will receive surgical excision of the keloid scar at the beginning of the procedure during skin incision. The baby will be delivered as normal, and routine wound closure will be performed in accordance with National Institute for Health and Care Excellence (NICE) guidelines as follows: The uterus is closed in two layers followed by closure of the rectus sheath, all using continuous sutures with 1-Vicryl (Johnson & Johnson). The fat layer is closed with interrupted plain gut sutures 2 cm apart. The skin layer is then closed with 3-0 Monocryl (Ethicon) in a sub-cuticular fashion.

The intervention group will receive surgical excision of the keloid scar after the delivery of the baby. Closure of the uterus layers, rectus sheath and the fat layer are completed as explained above. Then, triamcinolone acetone will be injected sub-dermally at the time of wound closure. Two ampules of triamcinolone acetonide (Kenacort®-A 10 suspension, Aspen Pharma Pty Ltd) will be administered at a single dose; each ampule contains 10 mg/1 ml active medication. The surgeon will inject one ampule along the entire length of the upper edge of the skin incision and one ampule along the entire length of the lower edge of the skin incision, using a 25 G needle.

After the procedure is completed, the surgeon will fill in the post-operation survey. The excision of the scar and administration of the injection will be performed by the surgeon who is scheduled to perform the surgery on that day. All the surgeons in the Department of Women’s and Newborn Health will be trained on how to perform the excision and injection of the triamcinolone. The Principal Investigator of the study will assess the fidelity to the intervention by supervising procedures.

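### The within-group χ² test of keloid counts treats the same women as independent samples and, if the reference is baseline, says nothing about the injection

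*Protocol article*

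**What the plan says.** All references are to the protocol article.

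- **Data analysis:** "Comparison of the number of patients with keloid formations within groups and between the two groups will be done using a" χ² test. No reference time is given for the within-group part, no paired method is named, and the general p < 0.05 rule applies without a descriptive label. The same section plans a relative risk with 95% CI and a χ² or Fisher test between the arms for binary outcomes.
- **Participants:** inclusion requires "presence of a keloid scar from a previous caesarean section", and exclusion covers "having a previous caesarean section with no keloid scar".
- **Procedures:** the comparator is also operated on: "The control group will receive surgical excision of the keloid scar at the beginning of the procedure during skin incision". The intervention arm has the keloid excised as well, then injected.
- **Follow-up:** "All measurements at baseline and follow-up visits will be performed by the same researcher". The visits are at 6 weeks, 6 months and 12 months.
- **Sample size:** 75 women per arm, to detect an increase in efficacy "from 45% in the excision followed by radiation group to 70% in the excision followed by intralesional triamcinolone acetonide and 5-fluorouracil group".
- **Background:** regrowth after surgical removal is put at 50–100% of cases.

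**The concern.** There are two separate defects.

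1. **Pairing.** The χ² test for a 2×2 table assumes two independent samples. A within-arm comparison over time counts each woman twice.
2. **A fixed starting point.** If the comparison is with baseline, the starting proportion is a constant of 100%, set by eligibility. Because the keloid is excised in both arms, the later proportion cannot rise and will usually be lower. The hypothesis of no change is true only if every woman's keloid recurs. Rejecting it reflects eligibility plus excision, not the injection, which is what this superiority trial is meant to test.

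The risk is one of reporting. The Hypothesis and the objectives describe the effect as that of excision combined with injection. A very small p-value in the intervention arm could be presented as support for that package, although the control arm may show much the same result.

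**Working it through.** **Planning figures.** For 45% against 70%, two-sided 5%, 80% power, the pooled formula gives 61 per arm without continuity correction and 68 with it. Then 68 × 1.10 = 74.8, so 75 per arm and 150 in total, as stated. The rates and arm size used below are therefore the plan's own.

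**Assumptions for the baseline reading.** The within-group reference is baseline, all 75 women in an arm are followed up, and efficacy means keloid-free. The protocol states none of these.

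**Test statistic.** With k keloid-free women at follow-up, the table is [75, 0] at baseline against [75 − k, k]. Pearson's χ² reduces to 150k / (150 − k). With continuity correction it is 150(k − 1)² / [k(150 − k)].

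- k = 3: 450/147 = 3.06, p = 0.080.
- k = 4: 600/146 = 4.11, p = 0.043. Corrected p = 0.13, Fisher p = 0.12.
- k = 5: corrected p = 0.069, Fisher p = 0.058.
- k = 6: 900/144 = 6.25, p = 0.012. Corrected 3750/864 = 4.34, p = 0.037; Fisher p = 0.028.
- k = 34 (45% of 75, control planning rate): 5100/116 = 44.0, p ≈ 3e-11.
- k = 52 (about 70% of 75, intervention planning rate): 7800/98 = 79.6, p ≈ 5e-19.

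The threshold is thus 4 of 75 (5.3%) uncorrected and 6 of 75 (8%) corrected or with Fisher. It stays at 4 and 6 with 67 women per arm.

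**Probability of p < 0.05.** The keloid-free count is binomial with 75 trials and probability 1 − recurrence. The last column supposes an inert injection, so that both arms share the same recurrence.

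| True recurrence | One arm, uncorrected | One arm, corrected or Fisher | Both arms, uncorrected |
|---|---|---|---|
| 55% | 1.00 | 1.00 | 1.00 |
| 80% | 0.9999 | 0.999 | 0.9999 |
| 90% | 0.95 | 0.77 | 0.90 |
| 95% | 0.52 | 0.17 | 0.27 |
| 98% | 0.06 | 0.004 | 0.004 |
| 100% | 0 | 0 | 0 |

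**Would a paired test against baseline help?** No. Every discordant pair goes the same way. Asymptotic McNemar gives χ² = k, significant from k = 4 (p = 0.0455). Exact McNemar gives p = 2 × 0.5^k, significant from k = 6 (p = 0.031). These are the same thresholds as above, so ignoring the pairing is not what produces significance here.

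**Where pairing does matter: between follow-up visits.** As an illustration, suppose keloids rise from 20 of 75 to 30 of 75, with all ten changes in one direction. The χ² for independent samples is 3.0, p = 0.083. Exact McNemar gives 2 × 0.5^10 = 0.002. In this case ignoring the pairing loses power.

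**The case against.** **The reference time is inferred.** This stands. With three follow-up visits, the within-group comparison could be between visits. The 75/75 starting point and every p-value computed from it would then fall away, leaving only the pairing defect. That is still enough: no within-arm comparison over time makes a test for independent samples correct.

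**Significance is not guaranteed.** A reader might infer that excision alone is bound to make both arms significant. The documents do not support that. The Background's regrowth range runs up to 100%; at 95% recurrence a single arm is significant with probability 0.52 uncorrected or 0.17 corrected, and at 100% never. The 45% planning rate also comes from excision with radiation, not excision alone, and the protocol does not define efficacy as absence of keloid.

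**The threshold of four is the most liberal version.** This also stands. Continuity correction or Fisher's test moves it to six, although the Fisher provision in Data analysis is written for comparisons between the groups.

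**No misuse is planned.** A reader might infer that efficacy is to be judged from within-arm p-values, or by comparing the two of them. Nothing in the protocol says so. The design is parallel-group superiority, the sample size targets a difference between the groups, and the between-arm relative risk, CI and test are specified. At the planning rates that comparison has about 88% power with 75 per arm, without continuity correction. This limits the seriousness of the point but does not make the within-group test valid.

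**Conclusion.** The point holds, with limits. As written, the within-group χ² is the wrong method for any comparison over time, because the data are paired. If the reference is baseline, which is the natural reading since the primary outcome is framed as a reduction after the intervention, the test is also uninformative about the injection. At the planning rates it would be significant in both arms almost surely even if the injection did nothing, given full follow-up and efficacy taken as keloid-free. That near-certainty weakens around 90% recurrence and is gone by about 95%.

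The two defects should be kept apart. Significance against baseline comes from the fixed starting proportion together with excision. Ignored pairing matters mainly between visits, where it usually costs power.

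This is a moderate flaw in a supplementary test. The between-arm analysis, on which the trial's conclusion should rest, is not affected.

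**What to change.** In Data analysis, remove the within-group significance test against baseline. Report each arm's proportion of women with keloid at follow-up with a 95% CI, and state that all efficacy conclusions rest on the between-arm relative risk, its 95% CI and the χ² or Fisher test already planned.

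If change within an arm between follow-up visits is of interest, name the visits compared, use a paired or repeated-measures method (McNemar or GEE), and label the result descriptive. Replacing the χ² with McNemar against baseline is not a remedy, for the reason shown in the working.

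The cost is about one sentence of the analysis section. No visit, measurement or sample size changes.
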